### Methods: intervention assignment

#### Allocation

The pregnant women are assigned to Stratum #1 or Stratum #2 as a function of the hemoglobin values in the baseline analysis of the study. They are, then, randomly assigned to 2 treatment groups to receive different iron supplements. The randomization is performed using centralized computer software, which is automatic and masked and applies to the electronic data collection forms, as well. The procedure for randomization is independent for each Stratum.

### Blinding

The study will be triple blind: the participant, the health-care professional, and the statistician. The treatment drug will be administered “blind” i.e. the doses are not identifiable since the packaging has the same format, presentation, and visual characteristics.

For Stratum #1, the treatments will be designated as A or B, and for Stratum #2 they will be designated as C or D.

The laboratory of MEIJI TEDEC FARMA, SA will be responsible for manufacturing, packaging and labeling the study medications.

Only MEIJI TEDEC FARMA, SA and the Clinical Pharmacology Service of the Vall d’Hebron Hospital in Barcelona will know the distribution codes and the composition of each of the treatments.

There would be no need for un-blinding except if an unexpected serious adverse event occurs. In which case, the pharmaco-vigilance staff of TEDEC-MEIJI FARMA S.A. will take responsibility for un-blinding and communicating the adverse event to the appropriate health authorities. TEDEC-Meiji Farma SA will not reveal the treatment codes until the end of the trial, when these data and the documents generated will be made available to the Principal Investigator (VA) and the Promoter (Jordi Gol i Gurina).

### Methods: data collection, management and analyses

#### Data collection methods

Midwifes will be responsible for data collection from the clinical history, and from the questionnaires. They will introduce the data into an electronic data collection format which will be monitored by an external service.

The ultrasound measurements will be conducted by two obstetricians using previously-standardized techniques.

The pregnancy

– Clinical history of the mother: date of birth, socio-economic status, parity, date of last menstruation, corrected date of last menstruation, estimated date of partum, risk factors during pregnancy, pregnancy planning, previous use of contraceptives, clinical antecedents, surgery and personal obstetric data, toxic habits, blood pressure, height, weight of the mother (self-reported at the recruitment visit and measured objectively at each clinical follow-up visit). Similar data from the father will be solicited.

– Questionnaire on iron supplement intake and of multi-vitamins, adherence to iron supplementation and possible adverse effects and concomitant treatments (Drugs_Q)

– Food Frequency Questionnaire (FFQ) validated by our research team [23]

– International Physical Activity Questionnaire (IPAQ) [24,25]

– State-Trait Anxiety Inventory (STAI) [26]

– Fagerstrom test to evaluate tobacco dependency (Fagerstrom_Q) [27]

– Edinburgh Postnatal Depression Scale (EPDS) [28,29]

– Parenting Stress Index (PSI) [30,31]

– Standard laboratory analyses: Hemogram: hemoglobin, mean corpuscular volume, hematocrit (Coulter, Hialeah, FL, USA)

– Biological samples for the measurement of biochemical parameters (ferritin, cortisol) and genetic polymorphisms (C282Y and H63D of the HFE gene)

#### The fetus

Ultrasound data

– Ultrasound #1: confirmation of the date of the last menstruation and date of gestation corrected for echography, prenatal diagnostics, chorion characteristics, amniotic fluid and determination of secondary markers

– Ultrasound #2: biometry, morphological evaluation, gender, position and presentation of the fetus, body and cardiac activity, characteristics of the placenta and umbilical cord, and status of the fetus

– Ultrasound #3: evaluation of fetal growth using biometry, body and cardiac activity, characteristics of the placenta, of the umbilical cord, and position and status of the fetus

The newborn

– Clinical history of the newborn (gender, status of the newborn, weight and height at birth) and anthropometric measurements of weight, height, head circumference at 40 days

– Bayley III scales: indices to evaluate mental and psychomotor development [32]

– Early Infancy Temperament Questionnaire (EITQ) [33]: test to evaluate behavior and temperament

#### Procedures for extraction, transfer and storage of biological samples

Blood samples will be collected in 2 tubes; 1 tube of 7.5 ml containing EDTA as anticoagulant and 1 tube of 7.5 ml without anticoagulant. The samples will be transported to the BioBank for immediate analyses to generate the hematology profile using the laboratory’s Coulter analyzer. In the BioBank, the samples will be prepared for storage. Before processing, the samples in the EDTA tubes will be inversion-mixed 10 times to ensure that the blood is well mixed before centrifugation at 4°C to separate plasma which will be stored in aliquots (500 μl) at -80°C for measurements described later. DNA will be extracted and stored at -80°C for subsequent genetic analyses. The tube without anticoagulant will be left without mixing for 30 minutes at room temperature to enable coagulation. The serum will be separated by centrifugation, distributed in aliquots of 500 μl and stored at -80°C.

The stored samples in the BioBank will be thawed at the end of the clinical study and processed simultaneously to minimize inter-batch variation:

1) Serum ferritin (immunochemiluminescence)

2) C-reactive protein (immunoturbidimetry)

3) Cortisol (immunochemiluminescence)

4) Genetic analyses (only in the first blood sample): mutation C282Y, H63D of the HFE gene (PCR and digestion with specific enzymes)

To control for possible bias, the intra- and inter-assay coefficients of variation will be calculated for all the measured variables. Values recommended by the “kit” manufacturers are accepted. All the biochemical determinations of all the samples in a series will be performed by the same person so as to minimize inter-assay variations in the longitudinal measurements of variables that are of interest to the investigators.

### Statistical methods

The description of the variables studied will be performed using conventional techniques. Variables with non-normal distribution will be transformed as necessary for normalization of distribution of values. The Kolmogorov-Smirnov and the Shapiro-Wilks test will be used to verify normality of distributions.

#### Analysis of the primary outcome

The effects of iron dose supplement in each RCT on the biochemical iron status and mother-child health will be compared using regression models adjusted for those variables that can influence the relationship. Logistic regression or Cox models will be applied for qualitative variables such as, for example, the percentage of anemia or hemoconcentration at the end of pregnancy. Linear multiple regression models will be applied for dependent quantitative variables. The models will be adjusted for those variables that biologically affect the relationships studied, such as the serum ferritin levels, presence of alterations in the HFE gene, age of the mother, gestational age, parity, anthropometric indices, diet, and lifestyle, and the interactions between these variables. Initially included in the model will be all those variables that form part of the theoretical model and, in a second phase, the variables for entry into the model will be selected step by step (forward and backward) to achieve the most reduced stable models.

Conditions for the application of models will be verified using standard techniques that are based, essentially, on residuals analysis. The bilateral null hypothesis of normality, no difference, and non-significance of the regression coefficients, will be rejected when their probabilities are <5%. The data will be analyzed using the latest version of SPSS/PC package for Windows.

Data will be analyzed in 2 ways:

a) Intention-to-treat analysis

The principle of “intention-to-treat” is a way of analyzing the results that considers all individuals entered into the study, according to the group to which they were originally assigned, although they may not have complied with the protocol. In this case, in all the circumstances that have led to not having hemoglobin determinations before delivery, we will proceed to incorporate at this time-point the immediately-prior determination of hemoglobin. All randomized participants randomized who had received at least one dose of study medication will be included.

b) Per-protocol analysis

Included in the analysis will be only those pregnant women who received the allocated intervention at randomization. The per-protocol population (PP) will include those participants who had taken at least the 80% of the study medication, with proper assessment of adherence, or without any major protocol violations.

Pregnant women diagnosed with anemia at the start will be treated according to the usual protocol, and not as a part of the current study. Women diagnosed with anemia posteriorly, will be treated with standard therapy, but will remain part of the study in the intention-to-treat analysis. However, they will not be considered in the per-protocol analysis.

Data missing from the study variables will be treated with the direct likelihood method [34] when no data is available. In these cases, the profile of pregnant women will be used to adjust the estimates of these parameters.

An analysis of sensitivity will be performed using a mixed model based on constraint-based patterns of missing values without dependence on the future to assess the robustness of the main results of the Mixed Model Repeated Measures against the possible transgression of random default assumption.

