#### Biological samples of the RCT

The blood extractions at visits 1, 3 and at birth, will be more than are normally taken for biological analyses in a RCT. This is because slightly larger amounts are required for subsequent analyses such as specialized biochemical measurements (ferritin, cortisol) and genetics (C282Y and H63D of the HFE gene). These samples will be treated and stored for subsequent analyses in the BioBank of the reference hospital of the participating PCCs.

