### Sample size

The principal variables taken into account in calculating the size of sample needed are iron deficiency anemia, risk of hemoconcentration in the third trimester of pregnancy, and birth weight of the baby.

To achieve the study’s main objective, sample size is calculated in accordance with the following parameters: an alpha risk of 0.05 and a beta risk of 0.20 in a one-tailed test of comparison. A drop-out rate of 35% is factored-in.

To calculate the sample size needed to reduce the prevalence of iron deficiency anemia and hemocentration risk by 10 points, we consulted previous data from our research group [5,6,8]. We had observed a prevalence of 23.5% of iron deficiency anemia in the 3rd trimester in pregnant women with Hb levels of 110-130 g/L in the first trimester and a prevalence of risk of hemoconcentration of 14.7% in the 3rd trimester of pregnant women who started pregnancy with Hb levels of 130–150 g/L.

We found that, in Stratum #1 of the RCT, it will be necessary to include 283 women in each group and in Stratum #2 of the RCT 156 women would be necessary in each group.

With respect to child development, to detect differences in weight of the newborn ≥200 g taking into account a standard deviation (SD) of 450 g [5], the estimation suggests that it will be necessary to have 106 women in each group.

Hence, the overall study sample is calculated as 878 women: 566 in Stratum #1 and 312 in Stratum #2.

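### The plan permits a Cox model for the percentage anemic or hemoconcentrated at the end of pregnancy, a visit status with no event time; with usual model-based standard errors that route loses a few points of power, and it should be struck out

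*Protocol article*

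**What the plan says.** In the protocol article, Analysis of the primary outcome names logistic regression first and then gives the alternative: "Cox models will be applied for qualitative variables such as, for example, the percentage of anemia or hemoconcentration at the end of pregnancy". Nothing says which of the two models applies to which outcome. The same section sets a two-sided 5% criterion for regression coefficients.

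Outcomes defines anemia, ferropenic anemia and hemoconcentration risk by hemoglobin (and, for ferropenic anemia, ferritin) cut-offs at the clinical visits. Participant timeline places the only third-trimester visit at about week 36.

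Sample size uses "an alpha risk of 0.05 and a beta risk of 0.20 in a one-tailed test of comparison" and aims to "reduce the prevalence of iron deficiency anemia and hemocentration risk by 10 points". Its starting values are third-trimester prevalences: "We had observed a prevalence of 23.5% of iron deficiency anemia in the 3rd trimester" for Stratum 1 and "a prevalence of risk of hemoconcentration of 14.7% in the 3rd trimester" for Stratum 2. It allows for 35% drop-out and arrives at 283 and 156 women per group.

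On ferritin, Biological samples of the RCT ties the larger samples to "The blood extractions at visits 1, 3 and at birth", so the week-24 visit is not on that list.

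**The concern.** Cox regression models the time at which an event occurs. The outcome named here is the proportion in a given state at the end of pregnancy, and the article defines no onset time for it. Any time entered would be either a constant or the date of the appointment.

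Two things are at stake. The permitted models estimate different quantities: a hazard ratio built on appointment dates is not the prevalence difference on which the trial was sized. They also differ in precision, so the same women and the same events can give a weaker test under one permitted option than under the other, and the text offers no rule for choosing.

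**Working it through.** **Step 1: reproduce the sizing.** Inputs from Sample size: 23.5% against 13.5% (23.5 − 10) in Stratum 1; 14.7% against 4.7% in Stratum 2; one-sided 5%; 80% power; 35% drop-out. The arcsine formula is n = 2(1.645 + 0.842)²/h², with h = 2·arcsin√p₁ − 2·arcsin√p₂.

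- Stratum 1: h = 1.0122 − 0.7525 = 0.2597, so n = 183.3; 183.3/0.65 = 282.02, rounded up to 283.
- Stratum 2: h = 0.7870 − 0.4371 = 0.3499, so n = 101.0; 101.0/0.65 = 155.4, rounded up to 156.

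Both printed figures are recovered. The sizing is therefore a comparison of two proportions at one time point, with 0.65 × 283 ≈ 184 and 0.65 × 156 ≈ 101 completers per arm.

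**Step 2: what Cox does with such data.** Let x₁ and x₂ be the numbers of positive women in two arms of n each, with one common time and Breslow ties. The partial likelihood is proportional to e^(βx₂)/(1 + e^β)^(x₁+x₂). Its maximum is at e^β = x₂/x₁, and the model-based variance of β is 1/x₁ + 1/x₂. The correct variance of the log ratio of two proportions is 1/x₁ + 1/x₂ − 2/n, that is, the sum of (1 − p)/(np). Cox leaves out the (1 − p) factor.

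- Stratum 1 (expected x = 43.2 and 24.8): model SE 0.252, true SE 0.229, about 10% too large.
- Stratum 2 (expected x = 14.8 and 4.7): model SE 0.527, true SE 0.508, about 4% too large.

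**Step 3: power at the planned completers.** Exact enumeration over both binomials, unadjusted, one-tailed 5%:

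| Test | Stratum 1, 184 per arm | Stratum 2, 101 per arm |
|---|---|---|
| Logistic, Wald | 79.8% | 78.4% |
| Pooled two-proportion | about 80% | 80.2% |
| Cox, common time, Wald | 74.4% | 74.5% |
| Cox, common time, score | about 75% | 77.0% |

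Restoring the −2/n term brings the Stratum 1 Cox Wald test back to 79.7%, which isolates the cause. With the term missing, about 213 completers per arm would be needed for 80%, against 184 (213/184 ≈ 1.16).

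**Step 4: true level at a common time.** With 23.5% in both arms, the critical value is in effect inflated by 1/√(1 − 0.235) = 1.143. A nominal two-sided 5% test then has a level of about 2 × [1 − Φ(1.96 × 1.143)] = 2.5%. Exact enumeration gives 2.4% (2.9% for the one-sided test).

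**Step 5: visit date as event time.** In simulations with dates assumed to vary by about a week and independently of status, Stratum 1 Cox power is 71–73% one-tailed. For Stratum 2, a run of 1,500 trials gave 71%; a repeat with 20,000 trials gave about 72.5% (Wald) and 74% (score). In that repeat the Stratum 1 level stayed near 5%. Here the test is not conservative: power is lost because appointment dates add noise.

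**The case against.** The strongest reply is that the loss is not a property of Cox as such. At a common time, Efron ties gave 80–81% in Stratum 1 simulations, exact ties behave similarly, and a robust variance also largely removes the loss. The article fixes no tie handling, time variable or variance. This stands, so the 74% must be stated conditionally.

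The calculation also uses completers. The intention-to-treat set keeps every randomized woman who took a dose and carries the previous hemoglobin forward. If the assumed rates held in all 283 and 156 per arm, Cox Wald power would be 89.6% and 90.5% one-tailed. These are upper figures: carrying values forward may dilute the effect, and the text describes it for hemoglobin only, not ferritin. The point that absolute power may be higher stands.

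A reader might infer that status is read only once, so that Cox could never apply. The documents do not support that for hemoglobin-only outcomes: hemoglobin is also taken at about week 24, and Participant withdrawal counts women who become anemic as therapeutic failures. Time to first anemia could be defined. It would be a different outcome from the end-of-pregnancy percentage, and the article does not define it. On the listed ferritin schedule, ferropenic anemia has only one on-treatment reading before delivery.

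Finally, logistic regression is named first, and a condensed article may leave the assignment of models to an analysis plan. But the sentence expressly offers Cox for this percentage. That is a choice stated badly, not a detail left out.

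**Conclusion.** The point holds in conditional form. The article permits a model that does not suit the outcome it names. With model-based standard errors and Breslow ties at a common time, intervals are about 10% too wide in Stratum 1 and 4% in Stratum 2, and the test is conservative. The power cost is about 5 points in Stratum 1 and 1 to 6 points in Stratum 2, depending on whether Wald or score tests are compared. With visit date as event time, power is a little lower still.

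A reader might go further and conclude that the trial has 74% power, or falls below 80% in both strata. The documents do not support that: logistic regression is equally permitted and keeps about the planned power, and the full intention-to-treat set could have more. Nor is there a risk of excess false positives from the tied-time version.

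The figures rest on the article's own rates and drop-out, no covariate adjustment, and the one-tailed test used for sizing. The two-sided test in the analysis section lowers power under either model (Stratum 1: 69.5% logistic, 61.5% Cox). Most of that fall comes from the mismatch in sidedness, which is a separate matter.

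**What to change.** Remove the Cox alternative for the end-of-pregnancy percentages. State that anemia, ferropenic anemia and hemoconcentration risk at the week-36 visit are analysed by logistic regression, with the risk difference and its confidence interval reported. If a risk ratio is preferred, use log-binomial regression or Poisson regression with robust variance.

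If a time-to-first-event outcome is wanted, define it separately, with its time origin, event time, censoring rule and handling of ties, and keep Cox for that outcome alone.

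The cost is one or two sentences. No new data, visits or women are needed, and logistic regression is already in the plan.

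### The Stratum 2 hemoconcentration model starts from covariates and interactions that about 20 to 30 events are too few to support

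*Protocol article*

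**What the plan says.** Under Sample size, the article plans with "an alpha risk of 0.05 and a beta risk of 0.20 in a one-tailed test of comparison". It states that "A drop-out rate of 35% is factored-in", takes "a prevalence of risk of hemoconcentration of 14.7% in the 3rd trimester" as the reference rate in women who start with high hemoglobin, and aims to "reduce the prevalence of iron deficiency anemia and hemocentration risk by 10 points". From this, "in Stratum #2 of the RCT 156 women would be necessary in each group", and the totals are "566 in Stratum #1 and 312 in Stratum #2".

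Under Analysis of the primary outcome, binary outcomes go into logistic or Cox models. These are adjusted for "the serum ferritin levels, presence of alterations in the HFE gene, age of the mother, gestational age, parity, anthropometric indices, diet, and lifestyle", together with "the interactions between these variables. Initially included in the model will be all those variables that form part of the theoretical model". The same sentence goes on to a second phase, in which forward and backward selection reduces the model to a smaller stable one. The intention-to-treat analysis keeps every randomized woman who took at least one dose and replaces a missing pre-delivery hemoglobin with the previous value. Tests are two-sided at 5%.

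**The concern.** The sample size rests on a plain comparison of two proportions and makes no allowance for a covariate model. The information in a logistic model for a rare outcome is limited by the number of events, and the plan's own rates make that number small in Stratum 2. A starting model with many interactions then invites separation: some coefficients run off to infinity and there is no usable dose estimate. Where the fit does converge, the dose odds ratio is pushed away from 1 and the test rejects too often. The article gives no rule for a starting model that cannot be fitted, so the analyst would have to improvise on a primary outcome.

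**Working it through.** **Reproducing the plan's sample size.** Inputs from Sample size: 14.7% against 14.7 − 10 = 4.7%, one-sided 0.05, power 0.80, drop-out 35%. The arcsine formula n = 2(z₀.₉₅ + z₀.₈₀)² / h², with h = 2·arcsin√0.147 − 2·arcsin√0.047, gives 101.0 completers per arm. Then 101.0 / 0.65 = 155.4, rounded up to 156. The same formula for 23.5% against 13.5% gives 282.01, rounded up to 283. Both stated sizes reproduce from an unadjusted comparison.

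**Expected Stratum 2 events.**
- Completers: 156 × 0.65 = 101.4 per arm; 101.4 × 0.147 + 101.4 × 0.047 = 14.9 + 4.8 = 19.7 (simulated 95% range 12 to 28).
- All randomized women at the same rates: 156 × (0.147 + 0.047) = 30.3.

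**Size of the starting model.** Assume one column per family, which is generous because diet and lifestyle are collected by questionnaires. Dose plus 8 main effects is 9 coefficients, or 19.7 / 9 = 2.2 events each. All pairwise interactions add 8 × 7 / 2 = 28, giving 37 coefficients, or 19.7 / 37 = 0.5 events each (30.3 / 37 = 0.8 with everyone analysed).

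**Fitting it.** Four simulation set-ups were used. They shared eight covariates at one column each and differed in coding details, covariate effects (none or modest) and convergence rule.
- *101 per arm, all pairwise interactions:* the model could not be fitted in about 28%, 40%, 49% and 68–74% of data sets.
- *Converged fits, 101 per arm (three set-ups):* the median dose log odds ratio was −1.89 to −2.08. The true value is ln(0.047/0.953) − ln(0.147/0.853) = −1.25. As odds ratios, that is about 0.12–0.15 against 0.29. With no dose effect, two-sided 5% tests rejected in about 8–12%.
- *156 per arm, same model:* failures of about 4%, 8% and 18–51%. In one set-up the median log odds ratio was still −1.62.
- *101 per arm, main effects only:* fitted in about 97–99%, with one-sided power of about 74–78%. Unadjusted power at 101 per arm is 77.9% by a standard two-proportion formula.

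**After selection, 101 per arm (one set-up, 500 data sets, dose forced in).** Of the backward-selected final models, 22% were still separated; of the forward-selected ones, 5%. One-sided power was 85% and 81%, counting rejections from all final models, separated ones included. With no dose effect at 9.7% in both arms (about 20 events), backward selection rejected in 16% two-sided and forward selection in 5%. At 14.7% in both arms (about 30 events), backward selection rejected in 6%. In a second set-up, backward elimination that stopped at any failed fit gave no result in 43–53% of completer data sets.

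**Stratum 1 for comparison.** 184 × (0.235 + 0.135) = 68 events; the same model converges in over 99%, with about 79% one-sided power.

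**The case against.** The strongest reply is that the starting model is not the reported one. The second phase reduces it, and the reduced model in completers reached about 81–85% one-sided power. A reader might infer that the trial loses its planned 80% power; the documents do not support that for the reduced model. What remains is that backward elimination begins from a fit that often does not exist, and about a fifth of its final models were still separated.

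Second, intention-to-treat is not limited to completers. Carrying hemoglobin forward keeps up to 312 women and about 30 events. Possibly more, because these women enter above 130 g/L and a carried-forward value may itself count as an event. Two set-ups then gave even the full model 85–87% one-sided power. This stands and makes the problem milder there. The per-protocol set, which drops poor adherers and women who become anemic, stays near 20 events or fewer.

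Third, the article does not say that all 28 pairwise terms enter, nor how covariates are coded; an unseen fuller document may do so. This also stands: the failure rates are conditional on that reading and vary widely with coding and convergence rules, so only ranges can be given. What the article does state, that interactions are included and all theoretical variables enter first, is enough for a narrower point.

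**Conclusion.** The point holds in limited form. For Stratum 2 hemoconcentration, a starting model with eight covariate families and their interactions is too large for about 20 events in completers, and strained at about 30. Under the all-pairwise, one-column assumption it fails in roughly 30–70% of completer data sets and in about 4–50% at 156 per arm. Where it fits in completers, it exaggerates the dose effect and rejects in about 8–12% instead of 5%. The prescribed selection does not reliably repair this. Fewer interactions would give a milder problem, and with none it almost disappears.

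It would be tempting to blame the covariates for the two-sided power shortfall in completers (67% unadjusted, 70–77% after selection). That gap comes mainly from sizing one-tailed and testing two-sided, which is a separate issue.

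**What to change.** For the Stratum 2 hemoconcentration outcome, and for other primary binary outcomes with similarly few events, state that the primary dose comparison is a logistic model with dose and a short list of baseline covariates named in advance, without interactions and without data-driven selection. Specify Firth penalised likelihood if separation occurs. Move the full covariate-and-interaction model to an analysis labelled exploratory.

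The cost is a change of wording in the analysis plan, with no new data and no change in sample size. The small downside is that some listed covariates would not be adjusted for in Stratum 2, where randomization within the stratum already protects against confounding.

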With respect to genetic alterations, the presence of the C282Y and H63D polymorphisms in the HFE gene have been associated with higher levels of hemoglobin [10,20]; a situation that can be aggravated if the individual is prescribed daily supplements of iron.

These factors (initial iron status and genetic alternations together with dietary intake and iron supplements) can explain the presence of different subpopulations of pregnant women, all having different iron needs during pregnancy. As a consequence, a prescribed iron dose modified to the individual’s characteristics would be needed to obtain optimum benefit.

There have been some studies that evaluated the effect of different doses of iron on iron deficiency as a function of the woman’s initial hemoglobin concentration but none, to the best of our knowledge, have also take into account possible iron excess and adverse effects on the newborn.

Hemoglobin is an ideal parameter to classify the women as a function of iron status, due to the high correlation with the levels of serum ferritin and with the presence of genetic alterations in the HFE gene. These measurements are relatively easy and quick, and are already used systematically in standard clinical practice, and in pregnancy follow-up.

Our hypotheses are that:

1) In women without anemia at the start of the pregnancy, with normal hemoglobin values of between 110–130 g/L, an iron intake of 40 or 80 mg/d, depending on the initial serum ferritin levels and on the presence of genetic alterations in the HFE gene, would be more effective in preventing iron deficiency, without increasing the risk of hemoconcentration by the end of pregnancy. This would help optimize mother-child health status.

2) In women without anemia and with normal-high values of hemoglobin of >130 g/L, an iron intake of 20 or 40 mg/d, depending on the initial serum ferritin levels and on the presence of genetic alterations in the HFE gene, will be more effective in ameliorating the risk of hemoconcentration by the end of the pregnancy, without leading to iron deficiency.

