### Outcomes

#### Primary outcomes

Principal variables in the pregnancy are iron status of the mother at each clinical visit (anemia, ferropenic anemia, risk of hemoconcentration) and birth weight of the baby.

Definition of main outcome variables

– Anemia is defined as Hb <110 g/L in the 1st and 3rd trimester, Hb <105 in 2nd trimester, Hb <120 g/L post-partum [21].

– Ferropenic anemia is defined as: Hb < the normal limit, and serum ferritin (SF) <15 μg/L [22].

– Hemoconcentration risk is defined as: Hb >130 g/L in the 2nd and 3rd trimester [4].

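### The primary models are reduced by stepwise selection from an open covariate list that is not limited to baseline values and does not secure the dose term

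*Protocol article*

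**What the plan says.** The Protocol article, section Analysis of the primary outcome, compares doses by logistic, Cox or linear regression, adjusted for variables "such as the serum ferritin levels, presence of alterations in the HFE gene, age of the mother, gestational age, parity, anthropometric indices, diet, and lifestyle". Interactions are added as well, without a list of which ones. All variables of a theoretical model enter first. After that, "the variables for entry into the model will be selected step by step (forward and backward) to achieve the most reduced stable models". The section gives no measurement time for any covariate, no entry or removal criterion, and no statement that dose is exempt from selection.

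Other sections bear on the point:

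- **Hypotheses (Background and rationale).** Both make the better dose one "depending on the initial serum ferritin levels and on the presence of genetic alterations in the HFE gene".
- **Biological samples of the RCT.** "The blood extractions at visits 1, 3 and at birth" are enlarged for assays that include ferritin, so both pre-treatment and on-treatment values will exist.
- **Primary outcomes.** Ferropenic anemia requires hemoglobin (Hb) below the limit together with ferritin below 15 μg/L. Birth weight is also a primary outcome.
- **Data collection methods.** Maternal weight is measured at each follow-up visit.

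**The concern.** In a randomised comparison the treatment contrast should come from a model fixed before the data are seen, adjusted only for things the treatment cannot have changed. The stated rule secures neither.

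- **Pathway variables can enter.** Ferritin at week 36 is a plausible route by which dose affects anemia or hemoconcentration. For ferropenic anemia it is also half of the outcome definition. Gestational age at delivery may lie between dose and birth weight; the Background links both anemia and hemoconcentration to premature birth. Adjusting for such variables removes part or all of the effect under test.
- **Dose may be subject to selection.** If it is, it is reported mainly when its estimate happens to be large.
- **Interactions are unlisted.** If dose-by-covariate terms are candidates, there are many chances of a false dose signal. If they are not, the dependence on ferritin and HFE status stated in the hypotheses has no secured test.

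Blinding the statistician does not prevent this. The group codes (A/B, C/D) are visible, so selection can still respond to a group difference.

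**Working it through.** **1. Evaluable numbers, from the plan's sample size.** Inputs from Sample size: 23.5% less 10 points = 13.5% (Stratum #1); 14.7% less 10 points = 4.7% (Stratum #2); one-tailed alpha 0.05, power 0.80, drop-out 35%.

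Arcsine formula: n = 2(z₀.₉₅ + z₀.₈₀)²/h², with h = 2·asin√p₁ − 2·asin√p₂ and (1.645 + 0.842)² ≈ 6.18.

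- Stratum #1: h = 0.260, n = 183.3; 183.3/0.65 = 282.01, rounded up to 283 (stated: 283).
- Stratum #2: h = 0.350, n = 101.0; 101.0/0.65 = 155.4, rounded up to 156 (stated: 156).

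The plan's figures are reproduced. Evaluable women per arm: about 184 and 101.

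**2. Effect on the model scale.** For 13.5% v 23.5%, the log-odds ratio is ln(0.135/0.865) − ln(0.235/0.765) = −1.857 + 1.180 = −0.68.

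**3. Simulation settings.** Logistic outcome, 184 per arm, eight background covariates, backward elimination at p<0.05 (assumed, since the plan gives no threshold), two-sided 5% test, 1,500 to 2,000 replicates. Monte Carlo standard error is about 0.5 points for error rates and 1 point for power. Reference power is below 80% because the sample size is one-tailed and the analysis bilateral, which is a separate matter.

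**4. Selection among baseline covariates**

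| Dose term | True log-OR | Rejects | Dose reported | Mean reported log-OR |
|---|---|---|---|---|
| Forced in | 0 | 5.1% | 100% | 0.01 |
| Selectable | 0 | 4.8% | 4.8% | −0.02 |
| Forced in | −0.68 | 73% | 100% | −0.70 |
| Selectable | −0.68 | 72% | 72% | −0.83 |

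Forced in, interval coverage is 95.0% under the null: selection does no visible damage. Selectable, exaggeration is 0.826/0.68 = 1.21, or about 21%, and under the null the few intervals reported never cover zero effect.

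The exaggeration depends on power. For birth weight with the plan's 200 g and SD 450 g at 101 per arm, SE = 450·√(2/101) = 63 g, power is about 88%, and the mean estimate given significance is about 214 g, or 7% too large.

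**5. On-treatment iron status as covariate.** Rates 22.3% v 12.9%, with the dose effect acting wholly through third-trimester iron status (assumed), dose forced in:

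| Iron-status covariate | Mean log-OR | Power |
|---|---|---|
| Baseline | −0.70 | 68% |
| On-treatment | 0.01 | 5% |

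Full mediation is the extreme; partial mediation falls between the rows.

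**6. Dose interactions as candidates.** With eight dose-by-covariate terms (assumed; the text does not say whether dose is among the interacting variables), the chance of at least one significant dose term under the null was 38–39%. As a rough check, nine independent 5% tests give 1 − 0.95⁹ = 37%.

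**7. Size of model the data can carry.** Expected events: Stratum #1, 184 × (0.235 + 0.135) = 68; Stratum #2, 101 × (0.147 + 0.047) = 19.6. Dose plus five single-term covariates is six parameters: 68/6 = 11 and 19.6/6 = 3.3 events per parameter. Nine further centre contrasts would leave 19.6/15 = 1.3 in Stratum #2.

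**The case against.** There are several good points on the plan's side.

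- **Timing.** The hypotheses speak of initial ferritin alongside HFE status, the same pair that opens the covariate list, so baseline ferritin is a natural reading. The list is described as variables that influence the relationship, not results of dose. For Hb outcomes, gestational age may simply mean age at sampling. This stands: a reader might infer that the plan intends post-dose adjustment, and the text does not say so. It only fails to rule it out.
- **Diet.** It is recorded repeatedly, so a reader might count it among variables changed by treatment. Nothing in the document suggests that a blinded iron dose alters diet.
- **Validity.** A reader might conclude that stepwise selection makes every p-value and interval invalid. Step 4 shows otherwise when dose is forced in and covariates are baseline. The harm needs dose or its interactions to be selectable, or a mediator to enter.
- **Dose as the comparison.** The section opens by saying that dose effects will be compared in adjusted models, which suggests that dose stays. This is likely but not stated.
- **Interactions.** It would be too strong to say that the effect-modification hypotheses go untested. Interactions are mentioned; whether dose is among them is ambiguous.
- **Detail left to an analysis plan.** Thresholds and time points often are. Stepwise selection, however, is a stated choice, and an analysis plan that follows the protocol would carry it over.
- **Which model is primary.** The end of the section refers to main results from a repeated-measures mixed model. That blurs which analysis is confirmatory but does not withdraw the stepwise rule, which sits under the primary-outcome heading.

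**Conclusion.** The concern holds in a limited form. The plan prescribes data-driven reduction of its primary models from an open list, neither limits covariates to baseline nor states that dose is retained, and so permits adjustment for variables between dose and outcome.

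The size depends on how the rule is applied. With baseline covariates and dose forced in, the cost for the dose test is negligible. If dose is selectable, its log-odds ratio is exaggerated by about 21% at the Stratum #1 design effect, and less for better-powered comparisons. If on-treatment iron status enters and carries the whole effect, power falls from about 68% to about 5%. Full mediation, the elimination threshold and the covariate structure are assumptions of the simulation; the sample sizes and approximate rates are the protocol's.

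**What to change.** Replace the two-phase selection in the primary analysis by one small pre-specified model per stratum:

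- Retain dose in every model.
- Use baseline covariates only, for example baseline Hb, visit-1 ferritin, HFE status, maternal age and parity. Keep the set shorter in Stratum #2, where about 20 events are expected, and do not add ten fixed centre effects.
- Exclude post-randomisation covariates, and report birth weight without adjustment for gestational age at delivery as the main result.
- Name dose × initial ferritin and dose × HFE status as secondary tests of the stated hypotheses, with confidence intervals and a note that power is low.
- Label any stepwise model exploratory.

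The cost is wording in the protocol and analysis plan; these covariates are already collected. The downside is that the fixed model may carry a few weak covariates and the interaction tests will seldom be conclusive.
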